### Recruitment process

People with PD will be recruited at the Neurological Clinic of Trieste University Hospital, while the research will be conducted at the ASUGI Physiotherapy Gym of the Trieste University. During a regular visit to the Movement Disorders outpatient clinic, the potentially suitable candidates will be invited to participate and will have the study design, protocol as well as all procedures and treatment of clinical data fully explained, as for standard institutional practice. The control group of neurotypical older adults will be recruited via the Daily Activities Center Koper, a database of previously enrolled subjects in the experiments of the Institute of Kinesiology, Science and Research Centre Koper, and via a word of mouth. The initial telephone screening in healthy adults (demographic and general health screening) will be performed to identify the potential participants. The identified participants will undergo a comprehensive screening session including motor and neurocognitive assessment (Measurement Day 1 - M1) to ensure they are meeting the inclusion criteria. Upon this confirmation, they will be invited to participate in Measurement Day 2 (M2). Participants will not be compensated for collaborating in the respective study in any way.

### Procedure, tasks, and stimuli

The study proposed by this protocol will consist of 2 measurement days per participant. Following the identification of potential participants (through clinical practice for people with PD and via initial telephone screening for healthy volunteers) they will be invited to the M1 meeting. The purpose of the M1 is twofold; first, to perform tests and apply questionnaires needed for checking the remaining of inclusion/exclusion criteria (MDS-UPDRS, Hoehn & Yahr Scale, MoCA, SPPB), and second, for successfully recruited participants the informed consent will be signed and other
*Supporting measures* will be taken from the participants (Demographic and general health questionnaires, SFES-I , FHS, TMT, BMIS, BDI, and for people with PD also N-FOG. No supporting measures will be taken should the potential participant not pass the inclusion criteria. The M1 for recruited participants will last approximately 1–1.5 hours. After the completion of the first measurement day, the fitting participants will be invited for the M2. These participants will be shown a recording of the M2 setting embedded within the actual environment with a fully equipped volunteer performing a DT walking condition. The recording will serve to familiarize the participants with the setting and address the potential anxiety of encountering new situations in a highly controlled environment. This will also be the opportunity to respond to participants’ questions and concerns.

The M2 will begin with the participant preparation; fixing EEG, HD-EMG, and full-body kinematic sensors on the participant. The order of motor activities, namely the overground walking, semi-tandem stance, and isometric force development, will remain fixed for all participants (see
Figure 1). The measurement day 2 will last approximately 5 hours. Below we specify the procedure of each motor activity and the associated cognitive tasks in more detail.

**
*Overground walking*.** After the resting state EEG recording (3 min with eyes closed and 3 min with eyes open), the baseline gait performance will be assessed by participants walking at self-selected speed but without carrying the response controllers in their hands along the 80 cm wide and 8m long lane for 3 minutes (excluding turn time). Then, the order of the ST and DT conditions will be randomized using a balanced Latin square formula for the 5 conditions, namely the ST-wide, DT-wide, ST-narrow, DT-narrow, and ST-visual conditions. In the visual discrimination task, the stimulus-response combinations will either share the side or not – ipsilateral or contralateral stimulus-response combinations, respectively (see
Table 1). A practice session will be conducted prior to each condition to ensure task comprehension and pacing familiarization.

**Table 1. T1:** Stimuli number of the cognitive visual discrimination task separated by motor task condition, hemifield presentation side, cognitive task modality, visual modality-specific properties, and presentation-response compatibility (in yellow).

		COGNITIVE TASK: Visual discrimination		
MOTOR TASK:	Presentation side:	Magenta	Cyan	∑
**ST-visual (Sitting)**	Left	30	30	60
	Right	30	30	60
**DT-wide (Walking)**	Left	60	60	120
	Right	60	60	120
**DT-narrow (Walking)**	Left	60	60	120
	Right	60	60	120
	**∑**	300	300	**600**
Correct response is	contra-lateral		Ipsilateral to the presentation side	

The ST-visual condition will be performed in the seated position in the middle of the walking lane while wearing response devices - VIVE pro controllers. In addition, participants will carry a custom-made spectacle frame with attached LED light on each end covering the periphery of the visual field, which will serve to provide visual stimulation. A total of 240 stimuli (120 magenta and 120 cyan) will be presented on either the left or right spectacle side (50–50%; see
Table 1 for stimuli characteristics). The interstimulus intervals will vary between 400–800 ms, and a response window will be limited to 900 ms after the stimulus presentation and indicated by pressing the button on the left- or right-hand held controller. The trial duration will vary between 1.4 to 1.8 s. Should no response be given within the predetermined response window, the next trial will start after 900 ms.

ST-wide and ST-narrow walking multimodal data will be collected while participants walk at self-selected speed in the wide (80 cm) and narrow (40 cm;
^
77
^) lane of 8 m length, respectively. The entire walking distance excluding the turn path will amount to 384 m (approximately 420 m including the turn path). Passing the end of the lane, a turn will follow, and a new gait pass will start upon re-entering the lane. Participants will be carrying response devices (VIVE pro controllers) although they will not be used in these two conditions. The estimated time for each condition is 7–8.5 minutes with turn times included.

In both DT-wide and DT-narrow walking conditions, the timing for visual stimuli presentation and responses will be the same as in the ST-visual condition. However, at the same time, participants will be walking along either a wide or narrow lane (described above) and upon reaching the end of the lane will be required to make a turn and re-enter the lane. The walking time of 7–8.5 minutes is estimated per condition (including the turn time). Per one lane length, 5 stimuli will be presented. The condition will end as soon as a participant walked 420 m (including the turn path) and 240 stimuli were presented.

Between each condition, a 2-min rest will be assured, during which NASA-TLX will be applied and participants will be asked to refer to the past condition. At the end of the 5 conditions of the walking activity, also the dual-task strategy assessment will be asked.

**
*Semi-tandem stance*.** Next, in semi-tandem postural experiment participants will perform three 30-second repetitions of semi-tandem stance for the ST-sts motor condition. This will be repeated in the DT-sts condition while simultaneously counting the occurrences of specific Stroop stimuli, and in the seated position for the ST-Stroop condition. The order of the ST and DT conditions will be counterbalanced across participants, however, the three 30-second repetitions of a certain condition will follow in succession in a fixed order.

Participants will be standing on a force plate (AMTI HE600600-2 k, Advanced Mechanical Technology, Inc., Watertown, MA, USA) in a semi-tandem position with their preferred (but always the same) foot in front and with their hands fixed on their hips. Over the 30-second runs in both ST-sts and DT-sts conditions, an average COP sway length (in cm) will be taken as an outcome measure. In DT-sts and ST-Stroop conditions the outcome measure will (also) be the reported number of the required observed Stroop-stimuli. In each of the three 30 sec repetitions, different combinations of Stroop stimuli will have to be attended, (e.g. “Blue” in blue ink, “Red” in red ink, and “Blue” in red ink). We choose silent counting of the Stroop-stimuli occurrences over loud to reduce the talking-related EEG artifacts. To motivate the participants into performing the cognitive task, they are required to report the result at the end of each 30-second trial. During the ST-sts condition, participants will be asked to direct their gaze to a fixation cross presented on the screen at the level of their eyes. 

**
*Isometric knee extension*.** Finally, for the trapezoidal isometric force tracking participants will undergo two 32-second force tracking sessions of knee extension (6 s rising phase, 20 s sustained phase, 6 s decline phase) per both right and left lower limbs in the ST-is motor condition. The participants will be sitting in a knee extension dynamometer (Wise technologies, Ljubljana, Slovenia) equipped with a force sensor and they will be instructed to actively contract their knee extensors to produce force up to 30% of their maximum voluntary contraction (MVC). The force tracking task will be repeated while concurrently performing the secondary serial-3 subtraction task quietly during the DT-is condition for both right and left lower limbs. The serial 3-subtraction task will also be quietly performed in an ST-sub condition for 32 seconds. Each time, a random 3-digit number between 300 and 500 will be selected as a starting point and at the end of the 32 second period, participants will be asked to report the number they had reached. The order of the right and left limbs and the ST-sub will be counterbalanced across the participants, while they will always perform the ST-is before the DT-is with a respective lower limb. The task will consist of 2 rounds of described conditions.

**
*Randomization sequence*.** The randomization sequence will be created via the online
balanced Latin square tool separately for each experiment.

### Data streaming and management

All data collected through paper-pencil tests and questionnaires will be digitized for further processing. Functional testing will be controlled through Unity3D (Unity Technologies, San Francisco, USA), which will also assign basic demographic data to each participant's measurement data. All functional measurements will be streamed and synchronized with the Lab Streaming Layer (Swartz Center for Computational Neuroscience, UCSD, USA). The synchronized data streams will comprise gait analysis (Motion Workshop, Seattle, WA, USA and VivePro, HTC, Taoyuan, TW), EEG (CGX, Cognionics Inc., San Diego, USA), and HD-EMG (OT Bioelettronica S.r.l., Torino, Italy) recordings, and secondary task performance (VivePro, HTC, Taoyuan, TW & Raspberry Pi, Raspberry Pi Foundation, Cambridge, UK). Day-to-day management of the study, including data management, will be coordinated by the principal investigator of the study. All data collected will be fully anonymized. Each participant will be assigned a unique study identification number. Access to the data will be restricted to TwinBrain researchers and staff, in possession of authorization rights. Directly identifiable data (e.g., name, address, phone number) are kept secure and separate from other study data. Data procedures will be in accordance with the General Data Protection Regulation (GDPR). In accordance with the Ethics Committee commitment, we will obtain informed consent from participants to share their anonymous data with other researchers. Data management will be regularly reviewed by an internal data monitoring committee composed of data experts, engineers, psychologists, and movement disorder physicians.

### Statistical analysis and power calculation

Descriptive data will be presented as means (M) and standard deviations (SD). The homogeneity of variances and normality of distribution of parameters will be tested with Levene's test and Shapiro-Wilk test, respectively. Using univariate analyses of variances (ANOVA), the between-subject factor grouping the sample will be
*PD* (early PD vs. no PD), while the within-subject factors will be the
*task complexity* (ST vs. DT) in each motor activity, i.e., the overground walking, semi-tandem stance, and isometric force knee extension, as well as the
*walking condition* (wide vs. narrow) for the overground walking only. Significance will be set at alpha = 0.05. The effect size will be presented as the unbiased adjusted partial eta squared
^
78
^. All post-hoc comparisons will control for multiple comparisons (e.g., Bonferroni). Statistical analyses will be done using SPSS (IBM, SPSS Inc, Chicago, IL, United States) or R (R Core Team, 2013).

Sample size estimation calculated using g*Power software (a priori: F-tests; ANOVA: repeated measures, within-between interaction; effect size f = 0.2; alpha error probability = 0.05; power (1-beta error probability) = 0.8; number of groups = 2; number of measurements = 3) revealed a total of
*N* = 42 subjects, half of who will be healthy older adults, and the other half will encompass people with early-stage PD.

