## Methods

### Trial design

This protocol is formulated according to the SPIRIT (Standard Protocol Items: Recommendations for Interventional Trials) statement
^
54
^. It describes a multifactorial mixed-measure design and encompasses three different motor activities. Specifically, the overground walking activity on a wide and a narrow path (ST -wide and ST -narrow) will constitute the core part of the study and will also be examined during a concurrent cognitive color discrimination task (DT -wide and DT -narrow); the cognitive task will additionally be examined in an ST condition for a comprehensive comparison (ST -visual). Second, postural control will be examined in the semi-tandem stance alone (ST -sts) and simultaneously with a cognitive task examining attention (DT -sts). The attention task will also be examined as ST in the seated position (ST -Stroop). Finally, in the seated position, isometric force development activity over time will again be examined alone (ST -is), under dual-task cognitive conditions while performing a series-3 subtraction task (DT -is), with the series-3 subtraction also performed in the absence of the motor task (ST -sub). In each motor activity, namely the overground walking, semi-tandem stance, and isometric contractions, one between-subject factor
*Group* (early PD vs. neurotypical older adults) and within-subject factor
*task complexity* (ST vs. DT) will be considered. In addition, in the walking activity, the second within-subject factor
*walking difficulty* (wide vs. narrow) will be implemented. This leads to a mixed between-within 2 (
*Group*) x 2 (
*task complexity*) study design for the isometric and stance activities and to a mixed between-within 2 (
*Group*) x 2 (
*task complexity*) x 2 (
*walking difficulty*) design for walking activity.
Figure 1 provides an overview of the study structure and timeline, as well as motor activities with ST and DT conditions embedded. We are aware that the direct comparison between the DT conditions of the three motor activities will not be possible due to the use of different cognitive tasks, yet this decision was motivated to avoid extensive learning effects and increasing frustration during the measurement day. A detailed description of the cognitive tasks and their respective stimuli can be found below under “Cognitive task performance”.

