*Managing adverse effect*.** The protocol and proposed experiments were modified after the pilot trials to minimize the occurrence of factors that led to experiment termination. Specifically, the number of stimuli and the duration of conditions were kept low enough to avoid fatigue but high enough to ensure adequate data quality, while the breaks between tasks/conditions were made sufficiently long. If reasons such as fatigue will nevertheless lead to a request for an interruption, the investigation will be terminated. Similarly, if participants will experience dizziness or will experience adverse effects for other reasons, the examination will be terminated. A physician will be present to ensure physical safety. The experimental day is organized in three experiments, so the recorded data will provide valuable insights despite the number of experiments completed.

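### Within each motor activity the stated ANOVA normally drops participants who stop partway; a mixed model would keep the conditions they completed

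*Protocol article*

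**What the plan says.** **Method.** In the protocol article, Statistical analysis and power calculation, the model is given as "Using univariate analyses of variances (ANOVA), the between-subject factor grouping the sample will be" PD status. The within-subject factors are task complexity (single or dual task) in each activity and, for walking only, lane width. Under Trial design the layout is a mixed 2 x 2 "study design for the isometric and stance activities and to a mixed between-within 2" x 2 x 2 layout for walking, which is called the core part of the study.

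**Early stops.** Under Managing adverse effect: "If reasons such as fatigue will nevertheless lead to a request for an interruption, the investigation will be terminated". Dizziness or another adverse effect also ends the examination. The same paragraph adds: "The experimental day is organized in three experiments, so the recorded data will provide valuable insights despite the number of experiments completed".

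**Order.** Under Procedure, tasks, and stimuli: "The order of motor activities, namely the overground walking, semi-tandem stance, and isometric force development, will remain fixed for all participants". Within walking, "the order of the ST and DT conditions will be randomized using a balanced Latin square formula for the 5 conditions". In the isometric activity both legs are tested, "while they will always perform the ST-is before the DT-is with a respective lower limb".

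**Sample size.** The computed N is 42 and the abstract gives 42 as the number to be recruited. No expected rate of incomplete sessions is stated.

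**The concern.** A conventional ANOVA with within-subject factors needs a value in every cell of the design being analysed. For walking that means four cells: single and dual task on the wide and on the narrow lane. A participant who completes two or three of these and then stops has usable walking data, but is normally absent from the walking ANOVA.

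The protocol treats early stops as a real possibility. Its reassurance about partial sessions concerns whole experiments completed, so it does not reach a stop inside one. At stake is precision in a study of 21 per group with no spare participants, where the protocol itself expects recruitment of early PD to be slow. There is also a risk, not a documented fact, that those who finish differ from those who do not.

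**Working it through.** **1. The plan's own figure.** Inputs from the power paragraph: f = 0.2, alpha 0.05, 2 groups, m = 3 measurements. Assumed, because not stated: correlation 0.5 and no sphericity correction.

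λ = f² × N × m / (1 − ρ) = 0.04 × 42 × 3 / 0.5 = 10.08; df1 = (2 − 1)(3 − 1) = 2; df2 = (42 − 2)(3 − 1) = 80. Noncentral F gives power 0.803, so N = 42 is reproduced. Correlations of 0.3 and 0.7 would give N = 58 and 26.

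**2. Deleting incomplete participants under the same calculation.**

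| Complete | Lost | Power (m = 3, as planned) | Power (m = 2) |
|---|---|---|---|
| 42 | 0% | 0.803 | 0.716 |
| 40 | 5% | 0.782 | 0.693 |
| 38 | 10% | 0.758 | 0.670 |
| 36 | 14% | 0.733 | 0.645 |
| 34 | 19% | 0.705 | 0.619 |

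The last column is shown because task complexity has two levels, not three. That is a separate matter. In either column any loss lowers power, and in the planned one any loss tabulated takes it below 0.80.

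**3. How much a mixed model recovers.** Not all of this loss comes back. Two assumed patterns of stopping within walking:

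- 17 of 21 PD and 20 of 21 controls complete (37 of 42; 12% lost). Completer variance relative to full data: (1/17 + 1/20) / (2/21) = 0.1088 / 0.0952 = 1.14.
- 15 of 21 and 19 of 21 complete (34 of 42; 19% lost). (1/15 + 1/19) / (2/21) = 0.1193 / 0.0952 = 1.25.

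Compared with a mixed model on all completed conditions, the completer analysis of the group-by-task contrast had:

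- with random stopping, about 5% more variance in the first pattern and 10 to 12% more in the second;
- in simulation with stopping more likely in worse performers (SD 1, correlation about 0.5, true effect 0.57 SD, 250 runs, similar completion rates), standard errors of 0.245 against 0.234 and 0.258 against 0.239. The variance ratios are (0.245/0.234)² = 1.10 and (0.258/0.239)² = 1.165.

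Power from these standard errors, using noncentral t with df 35 and 32 for completers and 40 assumed for the mixed model, is 0.62 against 0.66 and 0.57 against 0.64. With no missing cells the two analyses agree.

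**4. Bias.** The walking simulation showed little bias in the interaction for either method. A second, two-cell illustration assumes the single task is always seen, the dual task is missing for 20% of PD and 5% of controls, the correlation is 0.5 and the true group-by-task effect is −0.50 SD:

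| Stopping depends on | Complete-case | Mixed model |
|---|---|---|
| nothing (random) | −0.50 | −0.50 |
| observed single-task performance | −0.58 | −0.50 |
| the dual-task cost itself | −0.33 | −0.37 |

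The direction of bias depends on the mechanism, and the mixed model removes it only when stopping depends on what was observed.

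**The case against.** The strongest reply is that the article states no deletion rule. It is a condensed report, and handling of incomplete data may sit in a fuller plan. That is fair, and a missing rule is not the point raised here. The point is that the method the article does name makes poor use of the partial data it foresees. A univariate ANOVA can be fitted in R in long format without deletion, but that is not its usual use.

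Three stronger readings are tempting, and the documents do not support them:

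- *Anyone who misses any condition is lost.* The ANOVAs are per activity, so someone who stops after walking stays in the walking analysis. The seated cognitive single tasks are not cells of the motor ANOVAs. If the visual single task falls last in the random order, a person who stops after four walking conditions has all four motor cells.
- *The protocol contradicts its own promise about partial data.* The promise is tied to the three experiments of the day, and separate ANOVAs honour it.
- *The results will be biased towards fitter patients.* No stop rate is given, and an excess in PD is an assumption. Walking comes first, has 2-minute rests between conditions, and durations were reduced after piloting; entry requires Hoehn and Yahr of at most 2 and SPPB above 7. Completer selection is more plausible in the isometric activity, which is always last and runs single before dual task for each leg.

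It also stands that a mixed ANOVA is a valid analysis of these designs when data are complete.

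**Conclusion.** The point holds in a limited form. For stops inside an activity, the named ANOVA is a poor match to what the protocol foresees, and a better method is available at little cost. If roughly 10 to 20% of participants stop within walking, the completer analysis has about 5 to 15% more variance for the group-by-task contrast, or about 4 to 7 points of power in the illustration. If nobody stops, nothing is lost. These figures rest on assumed stop rates, a correlation of about 0.5 and simple stopping mechanisms. The case for change is mainly precision. Protection against selection is partial, and absent where stopping follows the unobserved dual-task cost. It is a cheap improvement, not an error that invalidates the plan.

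**What to change.** In Statistical analysis and power calculation, replace the ANOVA for each motor outcome by a linear mixed model:

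- Fixed effects: group, task complexity, walking difficulty (walking only) and their interactions.
- Random effects: a participant intercept and, for walking, participant-by-task and participant-by-walking-difficulty effects. A random intercept alone would not reproduce the separate error terms of the 2 x 2 x 2 ANOVA when data are complete.
- Estimation by REML with Kenward-Roger or Satterthwaite degrees of freedom.
- Data: every completed condition of every participant.

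Report incomplete sessions by group and reason, and keep the complete-case ANOVA as a sensitivity analysis.

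The cost is wording only; R is already named and no extra data are needed. The downside is that the random-effects structure must be fixed in advance, together with the order in which it would be simplified if the model does not converge.

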^. Investigating the interaction between motor and cognitive symptoms not only on behavioral and but also on neurophysiological levels in ecologically valid settings could greatly enhance our understanding of the underlying mechanism of ST and DT performance decline. Such investigations, however, have only recently been enabled by the Mobile Brain/Body Imaging (MoBI;
^
51–
53
^) approach. which will be used in the present study to investigate time-synchronized electroencephalographic (EEG) and electromyographic (EMG) recordings as well as body movements in multilevel approach to understanding cognitive-motor interactions and their neuromuscular signature. The aim of the present study is to investigate the early PD disease-specific changes and laterality of neuronal rhythms during the three motor activities that demand different levels of cognitive-motor resources, namely (1) overground walking (dynamic condition), (2) semi-tandem stance (standing static condition), and (3) sustained isometric contraction (seated static condition), each as motor ST but also in combination with certain cognitive tasks in DT conditions. This will allow systematic assessment and identification of motor and cognitive factors contributing to the symptomatology of PD.

Compared with healthy participants, we hypothesize that early PD will have poorer ST performance on cognitive and motor tasks and increased DT costs on all motor activities. Furthermore, we expect that performance impairments with increased neural recruitment will be most pronounced in the highest motor complexity condition (walking in the narrow pathway) and even more pronounced in the corresponding DT variant (DT -narrow).

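### N = 42 was computed for three repeated measurements, but the stance and isometric ANOVAs have two, so power there is about 72% at f = 0.2 (at the implied rho = 0.5), not 80%

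*Protocol article*

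**What the plan says.** The section Statistical analysis and power calculation gives the G*Power settings: "a priori: F-tests; ANOVA: repeated measures, within-between interaction; effect size f = 0.2; alpha error probability = 0.05", followed by "power (1-beta error probability) = 0.8; number of groups = 2; number of measurements = 3) revealed a total of" 42, split equally between early PD and healthy older adults. It states neither the correlation among repeated measures nor a sphericity correction.

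The same section plans ANOVAs with task complexity at two levels in each motor activity, and adds wide vs. narrow for walking only. Trial design agrees. It describes a 2 x 2 "study design for the isometric and stance activities and to a mixed between-within 2" x 2 x 2 design for walking.

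Trial design also says that "direct comparison between the DT conditions of the three motor activities will not be possible", because each activity uses a different cognitive task. For walking, "the cognitive task will additionally be examined in an ST condition for a comprehensive comparison (ST -visual").

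The Introduction hypothesises that "early PD will have poorer ST performance on cognitive and motor tasks and increased DT costs on all motor activities". Under Outcome measures, the dual-task effects in all three activities are the principal outcomes.

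**The concern.** The number of measurements sets both the numerator degrees of freedom and the noncentrality of the interaction test, so it must match the analysis. No ANOVA that the article describes has a within-subject factor with three levels: stance and isometric contraction have two cells, and walking has four cells from two 2-level factors. The article does not explain the 3.

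For the same f, more measurements per person give more power. Entering three where the analysis has two therefore overstates power. What is at stake is the 80% figure for the dual-task-cost hypothesis in two of the three activities. A reader who takes it at face value would give a non-significant Group x task result there more weight than the design supports.

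**Working it through.** **Inputs from the article:** f = 0.2, alpha = 0.05, target power 0.80, k = 2 groups, m = 3 measurements, N = 42 (21 per group).

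**Inputs assumed:** correlation rho = 0.5 and sphericity epsilon = 1.

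**Formulas** (G*Power, within-between interaction):
- lambda = f² x N x m x epsilon / (1 − rho)
- df1 = (k − 1)(m − 1) x epsilon
- df2 = (N − k)(m − 1) x epsilon
- power = probability that a noncentral F with these parameters exceeds the 5% critical value

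**Step 1: reproduce the stated N (m = 3).** At N = 42, lambda = 0.04 x 42 x 3 / 0.5 = 10.08 with df 2 and 80, and power is 0.803. At N = 40, power is 0.782. The smallest even N is therefore 42, as stated.

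**Step 2: is rho = 0.5 the implied input?** With epsilon = 1, rho = 0.4 would have given N = 50 and rho = 0.6 would have given 34. With rho = 0.5, epsilon = 0.9 would have given 46. The pair 0.5 and 1 is the simplest that returns 42, but not the only one. By the same formulas, rho = 0.6 with epsilon = 0.75 also returns 42.

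**Step 3: how many measurements does each outcome have?**

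| Outcome | Conditions in which it exists | m |
|---|---|---|
| Centre-of-pressure sway | ST-sts, DT-sts | 2 |
| Stroop count | ST-Stroop, DT-sts | 2 |
| Force deviation | ST-is, DT-is | 2 |
| Subtraction result | ST-sub, DT-is | 2 |
| Visual-task accuracy and response time | ST-visual, DT-wide, DT-narrow | 3 |
| Gait parameters | ST-wide, DT-wide, ST-narrow, DT-narrow | 4 (2 x 2) |

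The stance and isometric activities each have three recorded conditions, but no single outcome is measured in all three.

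**Step 4: recompute for m = 2, all else unchanged.** At N = 42, lambda = 0.04 x 42 x 2 / 0.5 = 6.72 with df 1 and 40, and power is 0.716. At N = 52, power is 0.807, so 52 would be needed for 80% at f = 0.2. At N = 42, power reaches 0.80 at f of about 0.222.

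On the change-score scale, with 21 per group, lambda = (21/2) x d². Hence f = 0.2 is d = √(6.72/10.5) = 0.80 SD of the change, and f = 0.222 is d = 0.80 x 0.222/0.2 = 0.89 SD.

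**Step 5: sensitivity to rho (m = 2, N = 42, f = 0.2).** Epsilon is 1 by definition with two levels.

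| rho | 0.3 | 0.4 | 0.5 | 0.6 | 0.7 |
|---|---|---|---|---|---|
| power | 0.57 | 0.64 | 0.72 | 0.81 | 0.90 |

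**The case against.** **The 3 may have a legitimate source.** Walking is described as the core of the study, the visual task has exactly three conditions, and the cognitive dual-task effect is among the principal outcomes. For a Group x 3 interaction on that task, m = 3 and N = 42 are right. This stands, and so it would be wrong to infer that the G*Power arithmetic is faulty. However, the article does not say that this is the basis, and a calculation for one task in walking does not carry over to stance or isometric contraction.

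**The 72% depends on an unstated rho.** This also stands. A true single-dual correlation of about 0.6 would restore 80%. But the article claims no such value, and a lower one makes the shortfall larger.

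**Treating the three activities as the levels does not rescue the figure.** The article itself rules out comparing their dual-task conditions directly.

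**Stronger readings that a reader might infer:**
- *The walking three-way interaction is badly underpowered.* At the article's own f = 0.2, with four equally correlated cells and one degree of freedom, lambda = 0.04 x 42 x 4 / 0.5 = 13.44 and power is about 95%. A shortfall appears only if the raw contrast is held at 0.8 SD, which for the three-way is f = 0.1, half the planned effect.
- *The calculation fails because it does not cover the single-task group difference or every other hypothesis.* Sizing a study on one effect is normal practice, and the article does not claim more.

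**How visual-task outcomes are modelled could be left to an analysis plan.** That is fair as to detail. Even so, the only model that the article gives for walking cannot be fitted to outcomes that do not exist in ST-wide or ST-narrow.

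**Conclusion.** The point holds for two of the three activities. The power calculation and the stated 2 x 2 designs for stance and isometric contraction do not match. Under the simplest inputs that reproduce N = 42 (f = 0.2, alpha 0.05, rho = 0.5, epsilon = 1), power there is about 72%. That is some 8 points below the stated figure, or a chance of missing the effect of about 28% rather than 20%. In terms of detectable effect, f moves from 0.20 to about 0.22, which is modest.

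This is a mismatch between an input and the design, not a computing error. A reader might infer that the study as a whole is underpowered or must enrol 52. The documents do not support that: the calculation fits the three-condition visual task, and the stance and isometric figure turns on a correlation that the article does not give.

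**What to change.** Keep N = 42 and amend the power paragraph to:
- state the assumed rho and epsilon;
- name the interaction to which the three-measurement calculation applies (if it is the visual task's ST-visual, DT-wide and DT-narrow, say so);
- restate power for the stance and isometric 2 x 2 ANOVAs. Suggested wording: with 21 per group and rho = 0.5, power for the Group x task interaction is about 72% for f = 0.2 and 80% for f = 0.22. If the sponsor has grounds for another rho, give that value and its power instead.

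For visual-task outcomes, state a 2 (Group) x 3 (ST-visual, DT-wide, DT-narrow) model in place of 2 x 2 x 2.

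The cost is wording only. The stated power becomes slightly less favourable, and no participants, visits or measurements are added. The Study status section reports six participants tested, so the change can be made early.
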